# Transfer of FRozen Encapsulated multi-donor Stool filtrate for active ulcerative Colitis (FRESCO): study protocol for a prospective, multicenter, double-blind, randomized, controlled trial

**DOI:** 10.1186/s13063-022-06095-1

**Published:** 2022-02-22

**Keywords:** Fecal microbiota transfer, Fecal microbiota transplantation, Ulcerative colitis, Randomized controlled trial

## Abstract

**Background:**

Ulcerative colitis (UC) is a chronic inflammatory bowel disease with significant morbidity and mortality. Although the precise cause remains unknown, disturbances in the intestinal microbial community have been linked to its pathogenesis. Randomized controlled trials in UC and relapsing *Clostridioides difficile* infection (CDI) have established fecal microbiota (FM) transfer (FMT) as an effective therapy. In this context, preliminary results indicated that the transfer of sterile fecal microbiota filtrates (<0.2 μm; FMF, FMFT) of donor stool also drives gastrointestinal microbiota changes and eliminates symptoms in CDI patients. However, along with the success of FMT, regulatory agencies issued safety alerts following reports of serious adverse events due to transmission of enteric pathogens through FMT. To reduce this risk, we established an extensive test protocol for our donors and quarantine regulations for the produced capsules, but alternative concepts are desirable.

**Methods:**

Our project is a randomized, controlled, longitudinal, prospective, three-arm, multicenter, double-blind study to determine the safety and efficacy of repeated long-term, multi-donor FM or FMF transfers compared to placebo using oral, frozen capsules in 174 randomized patients with mild to moderate active UC. The primary outcome will be clinical remission at week 12.

**Discussion:**

This proposal aims to examine (a) the efficacy of encapsulated transfer of FM and FMF as a therapy for mild to moderate UC, (b) the short- and long-term safety of FMT and FMFT in patients with UC, and (c) the microbial and immunologic changes that occur after FMT and FMFT to help understand how and why it affects inflammatory bowel disease.

**Trial registration:**

ClinicalTrials.govNCT03843385. DRKS (Deutsches Register für Klinische Studien) DRKS00020471

## Strengths of this study

This multicenter study is the first randomized three-armed placebo-controlled trial assessing the clinical efficacy of sterile fecal microbiota filtrate transfer (<0.2 μm; FMFT) for treating active ulcerative colitis compared with classical fecal microbiota transfer (FMT).Videotaped colonoscopy with biopsies will be performed at study entry and 12 weeks after randomization to assess endoscopic and histological inflammatory activity. Central reading of video recordings will be performed.Patient’s reported quality of life indices will be assessed.Use of oral, frozen, encapsulated fecal microbiota or fecal microbiota filtrate for long-term treatment may increase patients’ acceptance.

## Background

Ulcerative colitis (UC) is a progressive chronic inflammatory disease affecting the colon with significant morbidity and mortality. Its incidence has been increasing, and currently, the highest incidence is reported in Northern Europe (24.3 per 100.000) [1]. In Germany, about 170,000–210,000 patients are affected by UC [2]. A recently published meta-analysis demonstrated an increased standardized mortality ratio of 1.19 (95% confidence interval, 1.06–1.35) for UC patients compared to the general population [3]. Disturbances of the intestinal microbiota have been linked to the pathogenesis of UC, and in active UC, the microbiota profile differs in composition and is less diverse than that in healthy subjects [4–6]. The efficacy of FMT for recurrent CDI has spurred its application in UC. To date, a total of 26 studies (8 randomized studies, 18 cohort studies) with 587 patients with UC have been published in the last few years. Two of the 8 RCTs had negative results [7, 8], while six randomized, placebo-controlled trials had positive results [9–14]. Since the diversity of the donor microbiota and the number of taxa transferred was linked to the success of the therapy in post hoc analyses [15], a so-called multi-donor approach was chosen in recent studies in which the microbiota of different donors are pooled [10, 11]. New developments in FMT include the application of efficient frozen material [16] and the application of stool via capsules [17, 18]. Very recently, a pilot study suggests that daily encapsulated FMT may extend the durability of FMT-induced changes in the gut bacterial community structure and clinical response to FMT in UC [12]. However, larger trials should be performed to explore the benefits of FMT and to determine its long-term impacts on clinical parameters for UC.

An important issue of FMT is safety particularly in immunocompromised patients. Transfer of undefined living microorganisms entails uncontrollable risks for infections and other complications. Therefore, Schreiber and colleagues investigated whether a sterile filtrate of fecal microbiota (FMF) (containing bacterial debris, proteins, antimicrobial compounds, metabolic products, and nucleic acids) rather than intact bacteria could be used as an alternative strategy [19]. They demonstrated in a small cohort of five patients with recurrent CDI that FMF transfer (FMFT) was sufficient to restore normal bowel habits, to change the gastrointestinal microbiota, and to eliminate symptoms. As FMFT alone sufficiently altered microbial and viral community composition, it indicates that bacterial components, metabolites, or bacteriophages could mediate the effects of the classical transfer of the complete fecal microbiota. Therefore, FMFT may represent a highly attractive approach in immunocompromised patients with UC.

## Methods/design

### Study design

This is a randomized, controlled, longitudinal, prospective, three-arm, multicenter, double-blind study to determine the safety and efficacy of repeated long-term, multi-donor FMT or FMFT compared to placebo using oral, frozen capsules in 174 randomized patients with mild to moderate active UC. The primary outcome will be clinical remission at week 12.

### Intervention

In Germany, the Federal Institute for Drugs and Medical Devices (German: BfArM = Bundesinstitut für Arzneimittel und Medizinprodukte) and the leading Ethics committee of the Friedrich Schiller University Jena, together with the Ethics committees of the participating study sites, are responsible for protocol approval. If changes are made in the course of the trial, the affected documents are adapted accordingly. If any documents requiring approval are affected (e.g., the protocol), respective amendments are prepared and submitted to the federal authority and the ethics committees for approval. Only after receipt of the approval or positive vote, the procedures of the trial are adapted accordingly.

All protocol and GCP violations are documented together with the corresponding measures and reported to the sponsor’s authorized representative, who assesses the deviations and can evaluate them with additional measures if necessary. Major protocol deviations and GCP violations are immediately forwarded to the sponsor’s authorized representative and escalated to the sponsor if necessary. If any changes in the trial affect the contents of the study registries (clinicaltrials.gov and the German Registry for Clinical Studies; German: DRKS = Deutsches Register für Klinische Studien), these will be adapted accordingly.

The sponsor or sponsor’s legal representative is supported by the center for clinical studies (CCS) in the coordination of the trial. Here, the areas of data management, monitoring, biometrics, SAE, and project management are applied. Meetings of the above-mentioned areas will take place regularly during the course of the trial. The different areas of the CCS are available daily for the study centers, e.g., check the inclusion of patients in the study and do on-site monitoring and central monitoring strategies on a quarterly basis. There is also a quarterly risk review of the study. Additionally, a central study coordinator is available for all study sites and coordinates e.g. the request for the IMP from the manufacturer and the delivery of the IMP to the sites/patients. In the local study sites, the organization of the trial and the recruitment of patients under GCP conditions is carried out by local study coordinators and physicians. These are in close contact with the central study coordinator and the CCS.

During the conduct of the clinical trial, a weekly exchange takes place with all trial staff of the coordinating team involved (e.g., legal representative, project management, monitoring, data management, biometrics, pharmacovigilance, central study coordination, manufacturer, etc.). Significant study-relevant information, results, and measures are recorded. The possibility of escalation to the sponsor in case of critical and serious faults in the course of the trial is described in a CCS internal SOP.

An external Data Monitoring and Safety Board (DMSB), composed of 5 international experts in inflammatory bowel disease and one patient representative, will review the progress of the study. Interim reviews of safety data will be performed. Recommendations whether the nature, frequency, and severity of adverse effects associated with study treatment warrant the early termination of the study in the best interests of the participants, the study should continue as planned, or the study should continue with modifications will be provided by the DSMB. The initial meeting of the DMSB took place 6 months after the approval of the federal authority and before the beginning of the trial. It continues to be conducted at the time the study is approved (yearly), and in addition, at least every 6 months thereafter during the trial. The DMSB is independent from the sponsor and members declare that they have no competing interests.

The preparation of frozen capsules for FM-, FMF-, and placebo-treatment will be carried out in the pharmacy of the University Hospital Jena under GMP conditions. The consistent preparation of capsules is guaranteed by using concerted standard operating procedures and identical conditions according to one shared GMP certificate. This trial will be carried out in Germany at approximately 20 study sites (list of study sites and further information can be obtained from the principal investigator [name]. [name]). All study sites have the required experience in clinical studies in the field of chronic inflammatory bowel diseases and treat patients regularly. Patients who meet the inclusion criteria (see below) have to consent to the FRESCO study and will be randomized 1:1:1 to receive intensive dosing of multi-donor FMFT or classical FMT as therapeutic strategies or saline as a placebo comparator. Before randomization, a screening endoscopy (with collection of a biopsy) will be performed and videotaped for central reading. Stool samples will be taken for determination of fecal calprotectin level and microbiome and virome profiling. In addition, patients will be assessed for Inflammatory Bowel Disease Questionnaire (IBDQ) [20] and concomitant medication (CM), and a physical examination (PE) will be performed. Adverse events (AE) will be assessed using the Common Terminology Criteria for Adverse Events.

The prepared frozen capsules will be handed out and transferred to the patients in cooling boxes at study week 0 (start point) and week 6. The capsules need to be refrigerated (−15°C ± 5°C) by the patient in order to maintain the pharmacologic activity of FM and FMF. Patients will take 2 × 5 frozen capsules (morning/evening) on 5 consecutive days per week (5 days on and 2 days off; week 1–week 12) with cold liquid (e.g., water) (Fig. 1).

**Fig. 1 Fig1:**
[figure not shown]
Intervention scheme FRESCO study

### Patient population

#### Inclusion criteria

18–75 years oldWritten informed consentPrior endoscopic confirmation of active UC of at least 6 months *and* with a minimum disease extent of 15 cm from the anal vergeHaving active disease, defined with a Mayo Score between 4 and 10 and Mayo endoscopic subscore >1 at study entryMay be receiving the following drugs (subjects on these therapies must be willing to remain on stable doses for the noted times)Oral 5-ASA compounds provided the dose prescribed has been stable for at least 4 weeks prior to randomization; the dose must be stable for the first 12 weeks after randomizationAzathioprine, 6-MP, or MTX provided the dose prescribed has been stable for 8 weeks prior to randomization; the dose must be stable for the first 12 weeks after randomizationOral corticosteroid therapy (prednisone prescribed at a stable dose ≤ 20 mg/day or budesonide prescribed at a stable dose of ≤ 9 mg/day) provided the dose prescribed has been stable for 2 weeks prior to randomizationTopical therapy (foams, enema) with mesalazine or budesonide: the dose prescribed has been stable for 2 weeks prior to randomizationComplete vaccination against SARS-CoV-2 as recommended by the STIKOAbility to understand and willingness to sign informed consent document in patients whom the investigator believes can and will comply with the requirements of the protocol

#### Exclusion criteria

Crohn’s disease or indeterminate colitis or proctitis aloneAcute abdomen or other clinical emergencies requiring emergent management (e.g., bowel obstruction, perforation and/or abscess, previous bowel surgery)Concurrent gastrointestinal infectionsOther causes of diarrheaCongenital or acquired immunodeficiency, severe comorbidities (e.g., diabetes mellitus, cancer, systemic lupus, decompensated cirrhosis, recent malignancy in the last 3 years)Negative EBV/CMV serologyPregnancyPatients who are unable or unwilling to undergo colonoscopyPrevious treatment with anti-TNF, integrin, or IL12/IL23 antibodies within the last 8 weeksPrevious treatment with calcineurin or JAK inhibitors within the last 4 weeksSystemic antibiotic use within the last 8 weeksParticipation in a clinical trial within the last 3 monthsPrior history of FMT or FMFTProbiotic use within 14 days of the start dateNot ensuring frozen storage (−15°C ± 5°C) of the capsulesAddictive or other medical conditions or circumstances that do not allow the subject to appreciate the nature, significance, scope, and possible consequences of the clinical trialSigns of non-compliance of the participant

### Recruitment

The numerous inquiries about FMT from patients in different treatment centers express the high level of interest shown on this complementary form of treatment. The trial has a multicenter character, and all participating study sites carried out an individual sample size estimate in advance. Taking into account the inclusion and exclusion criteria, approximately 600 patients are suitable. Furthermore, study calls for example via different organizations and networks will increase the number of eligible patients. This strategy will ensure an adequate number of participants to achieve the planned sample size. The recruitment period is 2 years from the start of the trial. The study is conducted for patients who are able to give informed consent, after a physician of the study group provided oral and written information using the forms provided. The patient gets information about the screening and all further required measurements, the nature, significance, objective, duration, procedure, benefits, all risks and other aspects of the clinical trial, and the use of the investigational medicinal product (IMP). Only after the patient has given informed consent, screening for participation in the trial and the measurements required for this purpose can start.

### Randomization

The assignment of the patients to one of the 3 treatment arms is randomized. After initiation of each study site, patients will be consecutively screened and eligible patients who are willing to participate will be included in the FRESCO trial. The patients are stratified according to the study site and previous therapy with biologics (yes/no). Each study site receives a list of consecutive randomization numbers for each of the two strata relating to the treatment. These will be allocated in the order of arrival of the patient and documented in the electronic database (eCRF). The manufacturer keeps an unblinded list per study site and previous therapy with biologics (yes/no). Upon request by a study site, the manufacturer will prepare the trial medication for the patient according to the treatment specified in the randomization list. The patient is blinded with respect to the medication. To address “concealment of allocation,” the 1:1:1 randomization will be done centrally and each patient who is randomized and who received one of the compared treatments is part of the full analysis set and analyzed according to the ITT (intention to treat) principle. To achieve balanced distributions for pretreatment factors, we apply stratified (factor 1: no steroids/steroids/thiopurines/steroids and thiopurines; factor 2: “participating centre”) block randomization. Emergency unblinding takes place by calling the 24-h housekeeping service at the Clinic for Internal Medicine IV, Jena University Hospital.

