### Statistical analysis

The main analysis will be conducted in the full analysis set according to the intention-to-treat principle. Remission rates will be compared with a two-step hierarchical testing procedure. In a first step, a generalized linear mixed model (GLMM) with fixed effects treatment and steroid/thiopurine stratum and random effect site will be applied to test the null hypothesis H_0_ that no difference in remission rates will be observed between the groups against the alternative in which there will be a difference between the groups. In case of rejection of H_0_, the following tests will be performed in a hierarchical order:
The FMFT and FMT group combined versus placeboFMT versus placeboFMFT versus placeboFMFT versus FMT

by means of Wald statistic on a two-sided significance level of 0.05. The significance level is met by this hierarchical testing approach.

Further sensitivity analyses in a per-protocol set, explorative subgroup analyses according to stratification levels, and analyses of secondary parameters with a respective GLMM approach are described in detail in the study protocol.

In principle, all data will be analyzed at least by descriptive statistics, i.e., number of available and missing data, mean, standard deviation, minimum, quartiles, and maximum for metric data and frequency analysis for categories.

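### The Randomization section states two incompatible stratification schemes, and the primary model carries the factor of only one of them

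*Protocol article*

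**What the plan says.** The Randomization section of the protocol article describes the allocation strata twice.

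- **Site by prior biologics.** "The patients are stratified according to the study site and previous therapy with biologics (yes/no"). Two sentences on how allocation works repeat this. For the sites: "Each study site receives a list of consecutive randomization numbers for each of the two strata relating to the treatment". For the capsule manufacturer: "The manufacturer keeps an unblinded list per study site and previous therapy with biologics (yes/no").
- **Centre by steroid/thiopurine use.** Further down, the block randomisation is said to have participating centre as its second factor and, as its first, "factor 1: no steroids/steroids/thiopurines/steroids and thiopurines".

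The Statistical analysis section specifies the confirmatory model as a "generalized linear mixed model (GLMM) with fixed effects treatment and steroid/thiopurine stratum and random effect site". Prior biologics does not appear in it. The same section plans "explorative subgroup analyses according to stratification levels" without naming the factor, and refers to the study protocol for detail.

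**The concern.** Both statements are affirmative and in the present tense, they stand in the same section, and nothing in the article reconciles them. A reader cannot tell which factor governs the allocation of capsules.

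The primary analysis should reflect the randomisation that was carried out. The three sentences that describe the lists all point to prior biologics, whereas the model points to steroid/thiopurine use. If the lists are as described, the confirmatory model leaves out the factor that was balanced by design and adjusts for one that was not. The subgroup definition inherits the same ambiguity.

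What is at stake is pre-specification. With two candidate stratifiers in the published plan, the choice of covariate for the primary test can be made, or disputed, after data are seen. The allocation itself cannot be changed once patients have been randomised.

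**Working it through.** **1. The plan's own figure.** The Sample size section uses a 2×3 chi-square test with remission rates of 30%, 30% and 5%, alpha 0.05 and power 0.80.

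- Mean rate: (0.30 + 0.30 + 0.05)/3 = 0.2167.
- Noncentrality: λ = n × Σ(pᵢ − p̄)² / [p̄(1 − p̄)] = n × 0.04167/0.1697 = 0.2455n, with 2 degrees of freedom.
- n = 39 per arm: power 79.7%. n = 40: λ = 9.82, power 80.8%. So 3 × 40 = 120 is reproduced.
- Dropout of 30%: 40/0.70 = 57.1, rounded up to 58; 3 × 58 = 174 is reproduced.
- n = 58: λ = 14.24, power 93.2%, against 93% in Table 1.

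No stratification factor enters this calculation, so 174 stands under either scheme.

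**2. Can the two statements be the same scheme?** The article gives about 20 sites.

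| Scheme | Strata per site | Cells | Mean patients per cell |
|---|---|---|---|
| Site × prior biologics | 2 | 20 × 2 = 40 | 174/40 = 4.35 |
| Site × steroid/thiopurine | 4 | 20 × 4 = 80 | 174/80 = 2.2 |
| All crossed | 2 × 4 = 8 | 20 × 8 = 160 | 174/160 = 1.1 |

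The text on the site lists speaks of two strata. That fits the first row only, and the article nowhere says that the factors are crossed. The schemes also differ in practice: the smallest complete 1:1:1 block is 3, and the average cell in the second and third rows is smaller than that.

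**3. Does the model match?**

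| Lists actually used | Model with steroid/thiopurine stratum and random site | What is wrong |
|---|---|---|
| Biologics | Omits a randomisation factor | Model, and the block-randomisation sentence |
| Steroid/thiopurine | Matches | The three sentences on biologics and the lists |
| Both crossed | Omits a randomisation factor | Model, and the description of the lists |

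Some statement in the article has to be corrected in every row. Site is in both schemes and in the model, so the mismatch concerns the second factor only.

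**4. How much could omitting biologics matter?** The documents give neither the share of patients with prior biologics nor its association with remission. Both are assumed here.

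- *Simulation A.* 58 per arm, 23 of 58 (about 40%) with prior biologics in each arm, odds of remission lower by a factor of 1, 2 or 4 in those patients, no site effect, global logistic likelihood-ratio test. With a common rate of 20% (2,000 trials each), type I error was 4.4%, 5.4% and 4.55% without the biologics term and 4.4%, 5.7% and 5.4% with it. With rates of 30%, 30% and 5% (1,000 trials each), power was 97.8%, 98.3% and 97.9% without it and 97.8%, 98.3% and 98.2% with it, a difference of at most 0.3 points. Monte Carlo standard error of a 5% rate: √(0.05 × 0.95/2000) = 0.5 points.
- *Simulation B.* 35% prior biologics, odds ratio 0.45, stratified score test, 2,500 trials. In three settings with power near 98%, 88% and 81%, adding or omitting the term changed power by 0.4, 0.2 and 0.5 points. Only the size of these differences is used here, not their direction.

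Neither simulation fits the planned mixed model with Wald tests, and power in A is close to its ceiling. They indicate an order of magnitude and no more.

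**The case against.** The strongest reply is that this is a condensed article. Lists are generated from the full protocol and a list specification, and three sentences agree on biologics, so lists could be built. That stands against any inference that allocation cannot be carried out. It does not remove the contradiction, because condensing explains omissions and not two incompatible statements in one section.

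A reader might also infer more than the documents support:

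- *That the primary model is certainly wrong.* It is not. If the steroid/thiopurine scheme is the operative one, the model already matches.
- *That omitting biologics visibly inflates standard errors or costs power.* Theory predicts a small loss if the factor is prognostic, but the differences above are negligible and type I error shows no clear conservatism.
- *That the planned subgroups are on the wrong factor.* The Statistical analysis section names no factor for them. They follow whichever stratifier applies, so they are undetermined, and they are exploratory.
- *That the four levels cannot hold every patient.* Read literally, a patient on thiopurines alone fits both the first and third levels, but the natural reading is neither, steroids only, thiopurines only, both. Methotrexate users, who are eligible, can be placed by steroid status.
- *That both factors must be in the model whatever the scheme.* At the planning rates about 58 × 0.30 × 2 + 58 × 0.05 = 37.7 remissions are expected, about 3 of them on placebo. Adding a factor that was not used for stratification is a matter of preference.

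**Conclusion.** The contradiction is real and needs correcting: one section gives two stratification schemes that cannot both be true, and the confirmatory model follows only one. The mismatch with the analysis is conditional. It exists if the biologics lists are used or both factors are crossed, and it is absent if the steroid/thiopurine scheme is used, in which case the text on the lists is wrong.

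The size is small on the available evidence. The sample size of 174 does not change, site is handled under either scheme, and the effect on power is about 0.5 points or less. That last figure rests on an assumed 35–40% with prior biologics, assumed odds ratios down to 1/4, and simpler tests than the planned model. The reason to act is that allocation, primary model and subgroups must refer to the same pre-specified factor.

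**What to change.** 1. In the Randomization section, state the single scheme that generates the allocation lists, with its number of strata per site, and delete the other. If allocation has already begun, state the scheme actually used.
2. In the Statistical analysis section, make the fixed stratum effect of the mixed model exactly that factor, or both factors if both are used. Keep site as the random effect.
3. Define the stratification-level subgroups by the same factor or factors.
4. If the steroid/thiopurine scheme is kept, write its four levels so that they are mutually exclusive.
5. A factor not used for stratification may be added as a covariate if the sponsor wishes. It should then be labelled as such and specified in advance.

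The cost is a correction to the Randomization text, a check of the list specification against it and, if the biologics lists apply, one line of the model. The sample size and Table 1 are unaffected.
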